#### Therapist involvement

For participants in Group 2, at the end of weeks 1 and 5, a physical therapist will contact the patient by phone to review the exercise performance. They will implement a teach-back type approach to assess adherence/ health literacy, and address questions or concerns patients have with the education or exercise material. The therapist may suggest adjustments to the exercise program or additional resources to address individual needs/concerns. Phone calls should take approximately 15-30 mins each. To inform treatment fidelity, the therapist will complete a checklist following each call.

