#### Feasbility outcomes

• Recruitment Rate: We will proceed with the larger trial if we are able to recruit 90 participants within 24 months, and if at least 50% of eligible participants consent to participate.• Adherence: Adherence to the education program will be considered adequate if 80% of all participants in the intervention groups complete the full online program and report it on the log. Exercise programs will be considered adequate if 60% of participants in the intervention groups report exercise at least 3 times per week.• Content Acceptability: Content acceptability will be assessed using item 7 on the Surgurical Satisfaction Questionnaire, where acceptability will be considered adequate if 60% of participants were satistifed with the treatment (score of atleast 4/5 on item 7).• Study Acceptability: Study acceptability will be assessed using item 10 on the Surgurical Satisfaction Questionnaire, where acceptability will be considered adequate if 60% of participants were satistifed with the study (score of atleast 4/5 on item 10).• Treatment Fidelity: If 80% of the content was covered in 80% of phone calls fidelity checklist assessment, fidelity will be considered acceptable.

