## Plan for statistical analyses

Descriptive quantitative variables will be presented as means and standard deviations and the categorical variables will be presented as percentages. Following pilot study guidelines, criteria to progress from feasibility to definitive trial are listed in Table 2 below. Each primary feasibility outcome measure will be assessed separately, and overall progression will be determined by the worst-performing criterion. If all signals fall into the green zone, we will proceed to the trial without changes. If none of the signals fall into the red zone but at least one falls into the amber zone, the design of the trial procedures will be amended before proceeding to the definitive trial. If at least one signal falls into the red zone, we will not proceed to the definitive trial without making significant improvements to protocol and re-assessing feasibility.

**Table 2. table2-17589983251345393:** Progression criteria for feasibility.

	Proceed	Proceed with protocol amendment	Significant protocol amendment
Recruitment *N* = 90 in 12 months	15-16/ month and 50% eligible to participate	13-14/ month and 40% eligible to participate	<12 /month and 30% eligible to participate
Adherence	• 80% of all participants in the intervention groups complete the online program, and 60% report exercise at least 3 times per week	• 60% of all participants in the intervention groups complete the online program, and 40% report exercise at least 3 times per week	• 25% of all participants in the intervention groups complete the online program, and 25% report exercise at least 3 times per week
Content acceptability	• 60% of participants found the treatment useful and helpful with a score of 7/10	• 40% of participants found the treatment useful and helpful with a score of 7/10	• <40% of participants found the treatment useful and helpful with a score of 7/10
Study acceptability	• 60% of participants found the treatment delivery acceptable, and reported being likely to use this treatment again and recommend it to others with a VAS score of 7/10	• 40% of participants found the treatment delivery acceptable, and reported being likely to use this treatment again and recommend it to others with a VAS score of 7/10	• <40% of participants found the treatment delivery acceptable, and reported being likely to use this treatment again and recommend it to others with a VAS score of 7/10

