Fidelity of treatment	• If 80% of phone calls and recorded notes were documented on the checklist by the therapist	• If 60% of phone calls and recorded notes were documented on the checklist by the therapist	If <40% of phone calls and recorded notes were documented on the checklist by the therapist

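### Treatment fidelity means content covered in the outcomes text but calls documented in Tables 1 and 2, so the progression table can be green when the stated definition fails

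*Protocol article*

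**What the plan says.** The protocol article states the fidelity criterion in three places.

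- **Feasibility outcomes (Treatment Fidelity):** "If 80% of the content was covered in 80% of phone calls fidelity checklist assessment, fidelity will be considered acceptable". This has a bar within each call (content) and a bar across calls (share of calls).
- **Table 1 (Treatment fidelity) and Table 2 (green column), in the same words:** "If 80% of phone calls and recorded notes were documented on the checklist by the therapist".
- **Table 2, other columns:** amber is "If 60% of phone calls and recorded notes were documented on the checklist by the therapist" and red is "If <40% of phone calls and recorded notes were documented on the checklist by the therapist".

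Two other parts of the article give these criteria their effect. Plan for statistical analyses says that "criteria to progress from feasibility to definitive trial are listed in Table 2 below" and that "overall progression will be determined by the worst-performing criterion". Therapist involvement says how the data arise: "at the end of weeks 1 and 5, a physical therapist will contact the patient by phone to review the exercise performance", and "To inform treatment fidelity, the therapist will complete a checklist following each call".

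**The concern.** One rule measures what was delivered within a call. The other, read as written, measures whether the call and its notes were recorded. A call can satisfy the second and fail the first, and it is the second that carries the green, amber and red zones. If the content measure falls short, the article says only that fidelity is not acceptable and attaches no action to the shortfall.

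What is at stake is the contrast between the two PREPS arms. Under Trial design, therapist follow-up is what separates Group 2 from Group 1, and Sample size estimation sets a non-inferiority margin for comparing them in the full trial. If the calls have an effect but their content is thinly delivered, the two arms become more alike, and the comparison is pulled towards a finding of non-inferiority. A pilot is the place to notice this, and the progression table as worded may not.

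**Working it through.** The plan gives no calculated figure for this criterion, so there is none to reproduce. The check sets the two rules side by side and applies both to the planned calls.

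**Inputs**
- Participants in Group 2: 30 (Participants section).
- Calls per participant: 2, at the end of weeks 1 and 5 (Therapist involvement).
- Planned calls: 30 × 2 = 60.
- Threshold across calls, the same under both rules: 0.80 × 60 = 48 calls.

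**What each rule counts**
- Text rule: calls in which at least 80% of the content was covered. Acceptable if the count is 48 or more.
- Table 2 rule: calls and notes documented on the checklist. Green if the count is 48 or more.

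**Applying both rules**

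| Calls documented | Calls covering ≥80% of content | Table 2 | Text rule |
|---|---|---|---|
| 60 | 0 | green | fails |
| 60 | 30 | green | fails |
| 60 | 47 | green | fails |
| 48 | 0 | green | fails |
| 60 | 48 | green | met |

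The rules disagree whenever at least 48 calls are documented and fewer than 48 reach the content bar.

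**How easily this could happen.** Let q be the chance that a call covers at least 80% of the content. The article gives no value, so q is an assumption shown over a range. Take the 60 calls as independent with the same q, and assume all 60 are documented. The chance of meeting the text rule is P(X ≥ 48), with X binomial(60, q):

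| q | P(text rule met) | Table 2 |
|---|---|---|
| 0.5 | <0.001 | green |
| 0.6 | 0.001 | green |
| 0.7 | 0.057 | green |
| 0.8 | 0.576 | green |
| 0.9 | 0.994 | green |

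The last column follows from the assumption of full documentation; it is not a separate result.

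**Zones.** On 60 calls, Table 2's cut-offs are 48 (80%), 36 (60%) and 24 (40%). Reading 60% as the amber floor, 24 to 35 calls (40% to just under 60%) fall in no zone.

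**The case against.** The best reply is that the table wording is shorthand. The outcomes text assesses content from the fidelity checklist. If that form lists content items, documenting a call on it may loosely mean ticking what was covered, and the fault is then mainly loose wording. The form is in a Study Manual that is not shown, so this reading cannot be excluded. Even so, the tables state no content bar for a call, and someone applying Table 2 literally would not apply one. The conflict in the criterion stands.

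Three further objections have merit and limit the point.

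- A reader might infer that Table 2 cannot detect non-delivery at all. The article does not support that. A call never made produces no completed checklist and may lower the percentage, depending on whether planned or completed calls form the denominator. The gap concerns calls that took place but covered too little.
- A reader might also infer that documentation will be almost complete whatever was said. Completing a checklist after each call makes this plausible, but the article does not state it. The tables above assume it, and nothing in the article suggests that coverage will actually be low.
- The worst-criterion rule is written for primary feasibility outcomes, and the Introduction names recruitment and retention as primary. Fidelity is nevertheless a row of Table 2, so as written it enters the decision.

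It is also true that the outcomes text remains in force, so a content failure would still count as unacceptable fidelity. But the article would then hold two opposite verdicts on the same data without saying which prevails.

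**Conclusion.** The point holds as an internal contradiction in a progression criterion. The text requires 80% of content in 80% of calls; Tables 1 and 2 require only that 80% of calls and notes be documented. Table 2 carries the decision, so it can be green where the stated definition fails, and that definition has no graded zones. On the planned 60 calls, this occurs whenever 48 or more are documented and fewer than 48 reach the content bar. How likely that is depends on coverage and documentation rates that the article does not give. The contradiction itself rests on no assumption. It should be corrected before the pilot results are judged.

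**What to change.** Use one content-based measure in the Feasibility outcomes text, Table 1 and Table 2: the percentage of calls in which at least 80% of the checklist content was covered. Keep the existing green threshold (80% or more) and Table 2's 60% as the amber floor. The sponsor should choose the red boundary, and adjust amber if needed, so that the zones meet and the range from 40% to just under 60% is assigned. Where red should start is the sponsor's decision and does not follow from the conflict in definitions. State whether planned or completed calls form the denominator. Report checklist documentation completeness separately, as a process measure.

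The cost is a rewording of the two table rows and an alignment of the text. No new data should be needed, because the outcomes text already assesses content from a checklist completed after each call; this assumes that the form lists content in a way that can be scored. The downside is a somewhat harder criterion. Under the binomial assumption above, if each call has an 80% chance of reaching the content bar, the chance of green is 0.576.

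### The zones in Table 2 do not cover every possible result (clearest for fidelity, 40-59%), so the progression rule can return no decision

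*Protocol article*

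**What the plan says.** The section 'Plan for statistical analyses' grades each feasibility outcome separately and lets the worst-performing one decide. It then defines three situations: every signal green (go ahead unchanged); the middle case, "If none of the signals fall into the red zone but at least one falls into the amber zone" (amend, then go ahead); and at least one signal red (no definitive trial without significant improvement and a new feasibility assessment).

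The cut-offs are in Table 2:

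- **Fidelity.** Green: "If 80% of phone calls and recorded notes were documented on the checklist by the therapist". Amber: "If 60% of phone calls and recorded notes were documented on the checklist by the therapist". Red: "If <40% of phone calls and recorded notes were documented on the checklist by the therapist".
- **Adherence.** Green: "80% of all participants in the intervention groups complete the online program, and 60% report exercise at least 3 times per week". Amber: "60% of all participants in the intervention groups complete the online program, and 40% report exercise at least 3 times per week". Red: "25% of all participants in the intervention groups complete the online program, and 25% report exercise at least 3 times per week".
- **Recruitment.** Green: "15-16/ month and 50% eligible to participate". Amber is 13-14 per month with 40%. Red is below 12 per month with 30%. The row is labelled as 90 participants in 12 months.
- **Content and study acceptability.** 60% / 40% / below 40%.

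The section 'Feasibility outcomes' gives one adequacy threshold per criterion and no boundary between amber and red.

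**The concern.** A traffic-light rule works only if every possible result falls in exactly one zone. The two acceptability rows do this, because red starts directly below the amber figure. In the fidelity row red starts 20 percentage points below the amber figure. In the adherence row the red cell carries no inequality sign. The recruitment row has both features on a smaller scale.

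The pilot exists to decide whether, and in what form, the definitive trial goes ahead. If a result falls outside every zone, that decision is made after the data are seen, which pre-specified criteria are meant to prevent.

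**Working it through.** The plan gives no computed figure for these criteria, so there is none to reproduce. The check assigns each possible result to a zone, applies the rule, and finds how likely an ungraded result is.

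**Inputs.** The cut-offs are those of Table 2. The two PREPS arms hold 30 + 30 = 60 participants ('Participants'). Group 2 has two calls per participant, so 2 × 30 = 60 planned calls ('Therapist involvement'). Assumptions: no losses, every call made, and independent binomial outcomes. The true rates are also assumed; the protocol's own hypothesis for completion is 80%.

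**Step 1: zones.** Green and amber figures are read as lower bounds, and '<' as printed.

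| Criterion | Green | Amber | Red | No zone |
|---|---|---|---|---|
| Fidelity | ≥80% | 60-79% | <40% | 40-59% |
| Completion, red read as ≤25% | ≥80% | 60-79% | ≤25% | 26-59% |
| Completion, red read as ≥25% | ≥80% | 60-79% | 25-59% | <25% |
| Exercise, red read as ≤25% | ≥60% | 40-59% | ≤25% | 26-39% |
| Exercise, red read as ≥25% | ≥60% | 40-59% | 25-39% | <25% |
| Consent, red read as ≤30% | ≥50% | 40-49% | ≤30% | 31-39% |
| Consent, red read as ≥30% | ≥50% | 40-49% | 30-39% | <30% |
| Recruitment pace per month | ≥15 | from 13 | <12 | 12 to <13 |
| Acceptability (both rows) | ≥60% | 40-59% | <40% | none |

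Reading the fidelity amber figure as an upper bound does not close that row; the hole moves to 61-79%. Each limb of adherence is taken alone here, so the gaps do not come from the word 'and' joining the two limbs.

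**Step 2: the rule.** Take fidelity at 45%.

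- All other rows green: not all green, no amber, no red. None of the three rules applies.
- One other row amber: no red and at least one amber, so the literal rule is to amend and proceed, although fidelity is below its own amber figure.

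**Step 3: chance of an ungraded fidelity result.** 24/60 = 40% and 35/60 = 58%, so the gap is 24-35 documented calls. With X ~ Binomial(60, p), P(24 ≤ X ≤ 35) is:

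| True rate p | 40% | 50% | 55% | 60% | 70% | 80% |
|---|---|---|---|---|---|---|
| Chance | 55% | 88% | 73% | 44% | 3.6% | 0.01% |

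**Step 4: chance of an ungraded completion result, on both readings.** With red as 25% or less the gap is 16-35 of 60 (27-58%). With red as 25% or more it is 14 or fewer of 60 (23% or less).

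| True completion | 25% | 40% | 50% | 60% | 70% | 80% |
|---|---|---|---|---|---|---|
| Red = 25% or less | 43% | 99% | 92% | 44% | 3.6% | 0.01% |
| Red = 25% or more | 45% | 0.5% | 0.002% | <0.001% | <0.001% | <0.001% |

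For exercise with red as 25% or less, the gap is 16-23 of 60, with chance 69% at a true rate of 30% or 35%.

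**Step 5: recruitment pace.** 90 / 12 = 7.5 per month. The gap at 12 to <13 lies above the pace that the row's label needs, and 7.5 itself falls in the red pace zone.

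**The case against.** The strongest reply concerns adherence. The red cell has the same form as the green and amber cells, which are naturally read as floors. Read as a floor, red runs from 25% up to the amber figure, and completion of 45% is plainly red. This stands. A reader might infer that a pilot with middling completion would almost certainly get no decision, citing the 92% and 99% in the table. The document does not support that: those figures hold on one of two readings, and only for assumed true rates inside the gap. What remains is that neither reading covers the whole scale and the cell does not say which is meant.

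A reader might also infer that the rule is too lenient on a failing pilot. That presumes the ungraded range was meant as red. If amber was meant to extend down to the printed red limit, amending and proceeding is the intended action. Nor can an ungraded row lead to going ahead unchanged, since that needs every signal green. With no other row red, the open choice is between an amendment and a significant amendment with re-assessment.

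Finally, the pace gap is one unit wide and is not poor performance against 7.5 per month, so it adds little. The conflict between pace figures and row label is a separate inconsistency.

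None of this touches fidelity. That row has a single limb and a printed '<' sign, and leaves 40-59% ungraded.

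**Conclusion.** The point holds in this form: Table 2 does not grade every possible result, and the stated rule then gives either no action or one that depends on whether some other row happens to be amber. Fidelity at 40-59% is the firm case. Adherence and the consent rate are incomplete on either reading of a bare figure, with the place of the hole ambiguous. Recruitment pace has a minor gap.

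The practical size depends on true rates that the protocol cannot know. If fidelity is near the hoped-for 80%, the gap will almost never matter. If it is 50-60%, the chance of an ungraded result is 88% to 44%. These figures assume 60 calls made and binomial variation. The gaps themselves need no assumption about true rates.

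**What to change.** Rewrite the fidelity, adherence and recruitment rows as contiguous ranges with explicit inequality signs, as the acceptability rows already do in substance. Grade each limb of a paired criterion so that every value has a zone. There are two ways to close a row:

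1. Red is everything below the amber figure. Fidelity becomes ≥80% / 60-79% / <60%, completion the same, exercise ≥60% / 40-59% / <40%, and consent ≥50% / 40-49% / <40%.
2. Amber extends down to the printed red limit. Fidelity becomes ≥80% / 40-79% / <40%, with the 25% and 30% figures given a sign in the same way.

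The first is stricter than the printed red limits and the second more lenient. Which is intended is for the authors to state, before pilot data are seen. The pace cut-offs should be closed only after they are reconciled with the row label of 90 in 12 months (7.5 per month). Otherwise the edit would entrench thresholds that do not fit the target.

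The cost is an edit to three table rows, with no change to sample size, data collection or intervention.

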## Ethics and dissemination

This trial is designed to be more pragmatic than exploratory, in the hopes of the intervention to be adopted into practice and eventually expanded into other hospitals within the country. This study will be the first to address a program for both reverse and total shoulder replacement patients, as usually studies focus on lower limb replacements, and if they incorporate shoulder replacements, it is only on total anatomical shoulder replacements. Reverse and anatomical shoulder replacements vary in post-surgical outcomes; indicating the need to make sure the program is able to educate all patients, regardless of implant type.

This study was designed to be presented in English which may limit the external validity of this study. During our previous work, results indicated that majority of people receiving a total shoulder replacements at the HULC were English speaking. Future iterations of this work however can include translations to target a larger population.
